## 6. OBJECTIVES AND OUTCOME MEASURES

| Objectives                                                                                                                                                                                                                    | Outcome Measures                                                                                                                                                                                                                                                                                                               | Timepoint(s) of evaluation of this outcome measure (if applicable)                                                                                          |
|-------------------------------------------------------------------------------------------------------------------------------------------------------------------------------------------------------------------------------|--------------------------------------------------------------------------------------------------------------------------------------------------------------------------------------------------------------------------------------------------------------------------------------------------------------------------------|-------------------------------------------------------------------------------------------------------------------------------------------------------------|
| Primary Objective
To establish the kinetics of iron uptake into the heart, liver, spleen, kidney, skeletal muscle and blood following a single intravenous iron infusion (Ferric carboxymaltose, Ferinject, 1000mg) | Changes from baseline in cardiac structure and function (Cine MRI) and multi-organ magnetic resonance relaxometries ( $\Delta R1/R2/R2^*$ ) for each participant                                                                                                                                                               | Baseline, prior to infusion (day 1)
Timepoint 1- 3hr post infusion (day 1)
Timepoint 2- ~2 weeks post infusion
Timepoint 3- ~6 weeks post infusion |
| Secondary Objective
Determine the effects of iron infusion (Ferric carboxymaltose, Ferinject, 1000mg) on serum iron indices and serum markers of tissue iron damage.                                                | Change from baseline in: 
 
1. Serum iron indices: iron, ferritin, transferrin saturation, non-transferrin bound iron
 
2. Serum markers of tissue iron damage, including but not limited to lipid peroxidation markers malondialdehyde (MDA) and 4-Hydroxynonenal (HNE)
 
 | Baseline, prior to infusion (day 1)
Timepoint 1- 3hr post infusion (day 1)
Timepoint 2- ~2 weeks post infusion
Timepoint 3- ~6 weeks post infusion |

## 7. STUDY DESIGN

This is a prospective, observational, study exploring the kinetics of tissue iron uptake following intravenous iron infusion (Ferinject), received as part of standard clinical care in a group of iron-deficient patients.

Participants will be recruited through the Iron Deficiency Management Service, part of the Oxford University Hospitals NHS Foundation Trust (OUHFT) .

Participants will receive their intravenous iron infusion (Ferinject) as part of their standard clinical care by an NHS clinician. They will undergo all the study MRI scans and additional study procedures at the Oxford Centre for Clinical Magnetic Resonance Research (OCMR), which is based at the John Radcliffe Hospital and is part of the Division of Cardiovascular Medicine within the Radcliffe Department of Medicine at the University of Oxford.

A study flowchart is shown in Appendix A.

### Data and Sample Collection

**MRI** – MRI scans of the target organs of interest (such as heart, liver, spleen, kidney, blood and skeletal muscle) will be undertaken in OCMR at the JR Hospital, using established methods for cardiac Cine MRI and for measuring R1, R2 and R2\* relaxometries for tissues.

**Peripheral blood samples** – 20 ml (~4 teaspoons) of blood will be collected by a nurse for study investigations. A separate sample collected as part of standard clinical care will be obtained. Serum from study blood samples will be extracted and stored at -80C in OCMR for all participants. At the end of the study, study serum samples will be transported to the [name] Lab at the Department of Physiology, Anatomy and Genetics (DPAG), Part of the Medical Sciences Division of the University of Oxford (see section 9.10).

## 8. PARTICIPANT IDENTIFICATION

### 8.1. Study Participants

- Participant is willing and able to give informed consent for participation in the study.
- Aged 18 years or above.
- Anaemia (haemoglobin less than 120g/L for women and less than 130g/L for men) and/or confirmed iron deficiency (ferritin less than 100mcg/L and/or transferrin saturation less than 20%).
- Scheduled to receive intravenous iron (Ferinject) for correction of iron deficiency.

### 8.2. Exclusion Criteria

The participant may not enter the study if ANY of the following apply:

- Any MRI incompatible implants (e.g. cardiac, neuro, ocular implants, surgical clips, aneurysm clips, shrapnel/bullets)
- Pregnant or lactating participants

- Acute decompensated heart failure
- Unstable clinical status
- Any other medical conditions which would influence the reliability of the study results determined by the investigators.
- Any other contraindication to MRI to be confirmed by the qualified MRI operator, e.g. tattoos containing traces of metal.

## **9. PROTOCOL PROCEDURES**

A schedule of procedures is shown in Appendix B.

### **9.1. Recruitment**

Participants will be recruited from referrals to the Iron Deficiency Management Service, part of Oxford University Hospitals NHS Foundation Trust (OUHFT). This service receives referrals from multiple sources across Oxfordshire. Patient referrals will be screened by members of the NHS Clinical team at IDMS to identify potentially eligible participants. For further details see section 9.2 below.

### **9.2. Screening and Eligibility Assessment**

Eligible participants will be enrolled only if this would not cause any delay to their care.

#### **Screening procedure**

Patients referred to the IDMS are typically anaemic (haemoglobin less than 120g/L for women or 130g/L for men) and will have a ferritin less than 100 ug/L and/or transferrin saturation less than 20%. These tests are carried out as part of routine clinical care. All referrals to IDMS will be screened by a member of NHS clinical care team. Patients who would require intravenous iron and who are deemed eligible to participate in the study will be sent an invitation letter and patient information sheet. Few days later, a member of the NHS clinical care team at IDMS will contact the patient by telephone to check they have received the information and are happy to be contacted further about the study by a member of the study team. If they are, a member of the study team will telephone the patient to explain the study, and answer any questions the patients might have and check their eligibility. They will also ask the patient for the verbal consent to participate in the study. If verbal consent is received, the member of the study team will then arrange a suitable date for the participant to receive their intravenous iron infusion as part of their standard clinical care, normally within days and proceed with the study as described below.

### **9.3. Informed Consent**

A member of the study team will make telephone contact with eligible patients who have agreed to be contacted about this study. They will detail the exact nature of the study; what it will involve for the participant; the implications and constraints of the protocol; the known side effects and any risks involved in taking part. They will also clearly state that the participant is free to withdraw from the study at any time for any reason without prejudice to future care, without affecting their legal rights, and with no obligation to give the reason for withdrawal. The participant will be allowed as much time as wished

to consider the information, and the opportunity to question the member of study team, their GP or other independent parties to decide whether they will participate in the study. Verbal consent will be taken at this stage and recorded in the CRF and the patient's medical notes. Once verbal consent is given, the member of the NHS clinical care team at IDMS will arrange for the participant to be given their intravenous iron treatment, as per standard clinical care, by a member of the NHS clinical care team at the OCMR, which is part of the Oxford University Medical Sciences Division, and is physically located on the John Radcliffe Hospital site.

Written version of the Informed Consent form will be presented to the participant when they attend OCMR on day 1 of the study. This will be done by a suitably qualified and experienced member of the study team that has been authorised to do so by the Chief/Principal Investigator. Again, this member of study team will detail the exact nature of the study; what it will involve for the participant; the implications and constraints of the protocol; the known side effects and any risks involved in taking part. They will also clearly state that the participant is free to withdraw from the study at any time for any reason without prejudice to future care, without affecting their legal rights, and with no obligation to give the reason for withdrawal.

The participant must personally sign and date the latest approved version of the Informed Consent form before any study specific procedures are performed. One copy of the signed Informed Consent will be given to the participant and another copy will be added to the participant's medical notes. The original signed form will be retained at the study site.

#### **9.4. Enrolment**

This is a non-interventional observational study and as such does not involve randomisation. Enrolled participants will be allocated a unique study identification number.

#### **9.5. Blinding and code-breaking**

There is no blinding in this study.

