**Key question with safety implications**- We do not know how I.V iron formulations affect myocardial iron levels and cardiac function in the long term. Answering these questions is important for ensuring that correction of iron deficiency is not accompanied by myocardial iron toxicity. It is widely assumed that I.V iron formulations such as Ferinject (ferric carboxymaltose or FCM) are taken up and degraded by macrophages, allowing slow and controlled release of iron into the circulation, and subsequent loading onto the plasma iron chaperone transferrin for uptake by tissues. Most tissues can prevent excess iron accumulation by downregulating the levels of transferrin receptor expression (this is achieved through the iron-sensing function of iron-regulatory proteins IRPs). However, kinetic studies of plasma iron indices, together with the speed of manifestation of associated physiological effects demonstrate that FCM infusion results in rapid and physiologically-relevant rise in non-transferrin bound iron (NTBI) in the plasma. Excess NTBI in the plasma is dangerous because it is taken up by tissues through L-type and T-type calcium channels, which are not regulated by IRPs. These channels are highly expressed in the heart and it is well established that they are responsible for the iron overload cardiomyopathy that occurs in genetic disorders of iron overload such as hemochromatosis (where NTBI is also raised). In pre-clinical mouse models, we found that a patient-equivalent dose of intravenous iron resulted in ~400% increase in cardiac iron levels.

**Study rationale** - This is a pump-priming study to establish if the standard intravenous iron treatment, given as part of standard clinical care to correct iron deficiency, results in an acute rise in tissue iron levels, including myocardial iron at the early timepoints, which would be evidence for the direct, rapid unregulated route of iron uptake. It is an observational cohort study measuring changes in tissue iron levels from baseline following infusion of intravenous iron. Tissue iron levels will naturally vary between individuals. Because of this, the study will not use a placebo arm. Instead, it will measure changes against baseline tissue iron levels.

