### 11.1. Description of the Statistical Methods

The primary outcome is the absolute change from baseline in MR relaxivities R1, R2, R2\* at each timepoint post Ferinject infusion, according to the following formulae:

$$\Delta R1 = R1 \text{ (at timepoint x)} - R1 \text{ (at baseline)}$$

$$\Delta R2 = R2 \text{ (at timepoint x)} - R2 \text{ (at baseline)}$$

$$\Delta R2^* = R2^* \text{ (at timepoint x)} - R2^* \text{ (at baseline)}$$

R1, R2, R2\* values are calculated as inverse of T1, T2, T2\* relaxation times obtained by the MR relaxometry or mapping techniques. The results will be reported as time series of average values and standard deviations (median and IQR for nonparametric variables) at each timepoint post Ferinject infusion. The presence of statistically significant signal will be assessed using ANOVA.

The secondary outcome measure is the change from baseline in serum concentrations of iron indices (iron, transferrin saturation, ferritin and non-transferrin bound iron) and markers of tissue iron toxicity (MDA and 4-HNE). Results will be expressed both as absolute change from baseline and as percentage change relative to baseline.

Further exploratory analyses will be performed for possible interactions between the observed measures using correlations, crosscorrelations and pharmacodynamic modelling.

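### Section 9.5 rules out all blinding without excepting image analysis, so knowledge of timepoint can bias the uncontrolled MRI changes; reading coded, shuffled scans would reduce this at small cost

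*Protocol*

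**What the plan says.** Section 9.5 consists of one unqualified sentence: "There is no blinding in this study". No other section provides for masked reading of images.

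On the comparison, section 5 explains that tissue iron varies between people and continues: "Because of this, the study will not use a placebo arm. Instead, it will measure changes against baseline tissue iron levels". The synopsis lists no comparator.

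On the outcome, section 11.1 states: "The primary outcome is the absolute change from baseline in MR relaxivities R1, R2, R2\* at each timepoint post Ferinject infusion". It adds that R1, R2 and R2* "values are calculated as inverse of T1, T2, T2\* relaxation times obtained by the MR relaxometry or mapping techniques". Sections 3 and 6 also list cine measures of cardiac structure and function under the primary objective. For the test, section 11.1 says: "The presence of statistically significant signal will be assessed using ANOVA". Section 11.6 sets a two-sided 0.05 level.

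On the direction of interest, section 5 says that the study is to establish whether the infusion "results in an acute rise in tissue iron levels, including myocardial iron at the early timepoints".

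Section 11 says that no separate SAP is in use, and section 11.8 that the protocol's own analysis outline will be followed.

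**The concern.** An open infusion prevents masking of participants and treating staff. It does not prevent masking of the person who later analyses the images. Section 9.5 draws no such distinction.

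The design gives little protection if reading is affected by expectation. The primary quantity is a later read minus a baseline read, so a directional difference between the two goes straight into the result and looks the same as iron uptake. There is no comparison group against which it could be checked, and the direction of interest is stated in advance.

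The serum side is better protected. Sections 9.6.2 and 9.10 put iron, ferritin, transferrin and transferrin saturation on an automated analyser and test all participants and timepoints as a single batch. The protocol describes no comparable safeguard for the images, which carry the primary outcome.

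**Working it through.** **Inputs from the protocol**
- Participants: 12 (section 11.2), in 4 cohorts of 3 (section 9.6.2). 4 × 3 = 12, which agrees. Section 11.2 says that the number was not derived statistically, so there is no effect size, SD or power to reproduce.
- Scans per participant: 4 (baseline, 3 hours, 2 weeks, 6 weeks), so 12 × 4 = 48 in all.
- Level: two-sided 0.05 (section 11.6).

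**Assumption**
- A constant reader shift *b* is added to every post-infusion read, in units of the SD of the change from baseline. The protocol gives no value for *b*, and no SD that would convert it to relaxation-rate units. A range is therefore shown.

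**Check 1: one paired contrast, no true change.** The test statistic follows a noncentral t distribution with 11 degrees of freedom and noncentrality *b*√12. With the critical value t = 2.201,

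P(reject) = 1 − F(2.201; 11, *b*√12) + F(−2.201; 11, *b*√12).

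**Check 2: repeated-measures ANOVA.** 40,000 simulated studies were run with 12 participants, 4 timepoints, independent errors with SD 1/√2 (so that the change has SD 1), and the same shift at all three post-infusion timepoints. F was tested on 3 and 33 degrees of freedom.

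| Assumed shift *b* (SD of change) | *b*√12 | Paired test | ANOVA |
|---|---|---|---|
| 0 | 0 | 5.0% | 5.0% |
| 0.1 | 0.35 | 6.2% | 6.2% |
| 0.2 | 0.69 | 9.7% | not run |
| 0.3 | 1.04 | 15.8% | not run |
| 0.5 | 1.73 | 35.3% | 35.7% |

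A separate 20,000-run simulation of the paired test gave 9.7%, 16.1% and 35.0% at 0.2, 0.3 and 0.5 SD, in line with the exact values.

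**Scale.** With 12 participants the paired test has 80% power for a true change of 0.89 SD. A shift of 0.3 SD is 0.3/0.89 = 0.34, about a third, of that change. A shift of 0.5 SD is 0.5/0.89 = 0.56 of it.

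**After the fix.** If masking brought *b* to zero, the rate would return to 5.0%. No sample size or power figure changes.

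**The case against.** **The sentence may mean only that nothing is allocated.** It comes directly after section 9.4, which says that there is no randomisation. A reader might infer that scans are read with full knowledge of timepoint. The documents do not say so: who reads, in what order, with what labels and with how much automation is not described. That limits the claim to a possible bias. It does not make the sentence adequate, because the wording is unqualified and section 11 points to no other document that would settle the matter.

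**The mechanism is not in the text.** Placing regions, contouring and rejecting poor images are not mentioned, and section 11.1 describes a calculation. This stands: the reader-dependent part of these values is unknown.

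**The sizes are assumed.** Any constant bias raises the rejection rate, and nothing in the protocol makes 0.2 to 0.5 SD more likely than 0.1 SD. This also stands. The table shows sensitivity, not an estimate.

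**Not every change from baseline is exposed.** A reader might infer that all outcomes are affected. The automated serum iron indices involve no image reader.

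**Masking is neither complete nor free.** Marked liver or spleen signal change may reveal the visit. One participant per cohort, so 4 of 12, has an extended baseline scan of up to 3 hours (sections 9.6.2 and 9.7) that may be recognisable. That scan also tunes the acquisition, which stays unmasked. The look after cohort 1 (section 11.4) is meant to judge the timepoints and so needs them decoded. These points shape the fix but do not defend leaving image analysis unmasked.

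**A control arm would not cure this alone.** It would cancel expectation bias only if readers were also masked to arm. That is correct, and masked reading equally does not stand in for a control.

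**This is a small pump-priming study.** True, and no confirmatory claim rests on one p-value. But its results are meant to inform a larger study (section 2), and the change asked for is small.

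**Conclusion.** The point holds as a design weakness that should be corrected. Section 9.5 excludes masking of image analysis along with everything else, in an uncontrolled study whose primary outcome is a within-person MRI change in a direction named in advance. Where reading involves judgement, knowledge of timepoint can bias the relaxometry and cine changes.

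The size is unknown. If the shift were 0.2, 0.3 or 0.5 SD of the change, the false-positive rate per contrast would be about 10%, 16% or 35% in place of 5%. This assumes a constant shift, no true change and 12 complete participants.

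The documents do not support saying that bias is present, that it reaches the serum iron indices, or that masked reading would abolish it.

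**What to change.** Replace the sentence in section 9.5 with:

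> The infusion is open-label. Relaxometry and cine analysis is done on scans stripped of identity, date and visit, randomly coded and shuffled, by a reader masked to timepoint and serum results; values are locked before decoding. For the extended baseline scans, only the standard-protocol images enter the masked worklist. Cohort 1 is read coded, locked and decoded separately for the interim look, and its scans are re-coded and re-read masked with the remaining cohorts for the final analysis.

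The cost is de-identification, a shuffled worklist and a re-read of cohort 1 (3 participants × 4 scans = 12 of the 48 scans). No additional reader or scan is needed.

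The report should state what this leaves open: some visits may still be recognisable from the liver or spleen, acquisition is unmasked, and scanner drift and other time effects are not addressed.

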#### **9.6. Description of study intervention(s), comparators and study procedures (clinical)**

##### **9.6.1. Description of study intervention(s)**

There are no interventions as part of this study. Intravenous iron infusion (Ferinject) is delivered as part of standard clinical care.

##### **9.6.2. Description of study procedure(s)**

### ***Magnetic Resonance Imaging***

#### **Overview**

MRI will be performed on clinical standard MRI scanners in OCMR (at conventional field strength 1.5 Tesla for this study). Participants will be grouped into 4 cohorts of 3, so that all participants in the same cohorts are scanned on the same days. Details of how cohorts will be run are shown in section 9.7 and in Appendix D. Each scan will consist of MRI scanning techniques to assess cardiac structure and function by Cine MRI and organ tissue characterisation using R1/R2/R2\* relaxometry.

The average duration of each MRI scan is envisaged to be around an hour. One participant in each cohort will be chosen to have an extended MRI scan at their first visit, lasting up to 3 hours. This extended MRI scan is needed to optimize the parameters for running of subsequent scans that day. All subsequent scans will be a standard duration of about an hour. This will be communicated to the participants clearly in the PIL and again on day 1 when they attend OCMR for their first scan.

### **MRI safety**

MRI is safe and non-invasive and does not involve any ionising radiation (x-rays). However, there are some contraindications. Because of this, participants will be asked pre-screening questions at the recruitment stage by a member of the study team, and again by the radiographer when they attend OCMR on day 1, prior to any procedures. Screening questions will check that the participant is not pregnant, or suspected to be pregnant, does not have claustrophobia, or carry heart pacemaker, mechanical heart valve, mechanical implant such as an aneurysm clip, hip replacement, or any other pieces of metal that have accidentally entered the body. Additionally, some types of tattoo ink contains traces of metal, but most tattoos are safe in an MRI scanner. Participants will be asked to change into pocketless and metal free "pyjama-style" top and trousers, available in a range of sizes, and will also be asked to remove underwired bras, metal jewellery, body piercings, and make up where applicable. Lockers are provided to secure their personal belongings and clothing. During the scan, participants will additionally be given earplugs, head padding or headphones to reduce the noise perception from the MRI scan, and will have a call button in their hands to alert the radiographer immediately if they feel heat in their tattoo, or any other general discomfort.

The OCMR is fully equipped for resuscitation (including defibrillation) in the unlikely event of a medical emergency during scanning, and doctors performing and/or supervising the scans are trained in magnetic safety, evacuation procedures, and either Basic Life Support (BLS), Intermediate Life Support (ILS) or Advanced Life Support (ALS).

